Patients receiving the intervention will be contacted by the researcher, via the telephone, 6 weeks after their review consultation to elicit their perceived progress in implementing their plans and perceived efficacy of the plans in achieving associated goals. Follow-up outcome questionnaires will be completed at 3 months and again at 6 months post review for all patients. Patients will have the option of receiving these by post and completing it themselves, or to complete them via the telephone with a researcher. The former will be supported by a telephone reminder to patients where necessary.

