### Withdrawal of patients from the study

There are five points at which consenting patients could withdraw from the study:

(1) prior to completing baseline questionnaires

(2) prior to attending the asthma review appointment with the practice nurse

(3) prior to the 6-week telephone follow-up

(4) prior to completing the 3-month follow-up questionnaires

(5) prior to completing the 6-month follow-up questionnaires

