### Statistical analysis

Data analysis, using the following analysis plan, will be undertaken blind to the allocation arm. The primary analysis will be a per protocol analysis based on an intention to treat [44].

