#### Comparison between treatment arms

The difference in the validated mAQLQ score between the intervention and control groups at baseline and 3 and 6 months post-intervention will be compared, adjusting for practice level stratum (region and list size). A clinically relevant improvement is an increase of ≥0.5 in individual mAQLQ mean scores [35]. Quality of life using the validated mAQLQ was measured at the baseline (January to May 2013) prior to the HCP asthma review appointment, and repeated at 3 months and 6 months post-intervention. Comparison of the mAQLQ scores at 3 months post-intervention as well as at 6 months post-intervention will enable us to establish the most appropriate time point for assessment of clinical endpoints. Changes from baseline to six months post intervention will be assessed in SPSS for Windows using multiple regression analysis with 6-month mAQLQ as outcome and baseline mAQLQ as covariate along with arm of trial (intervention/control) in the model. We will be adjusting all models for clustering within practices and matching by size. Transformations of the outcome variables will be used where necessary if these are not normally distributed. All analyses will be stratified by the stratification factors. We will estimate an ICC for all potential outcomes in the full trial. Consequently sample size estimates will be made for the full trial.

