### Missing data

#### mAQLQs

The mAQLQ is divided into four domains, with varying numbers of questions per domain, and the overall mAQLQ score is calculated from the mean of each domain [35]. Where more than one response is missing in the symptom or activity domains and any response missing in the emotional function or environmental domains, this patient will be excluded from the analysis [46].

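### The 6-month regression leaves out patients who withdraw after 3 months despite their 3-month mAQLQ, and can bias the estimated difference if that withdrawal depends on early response differently by arm

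*Protocol article*

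**What the plan says.** All references are to the protocol article; no separate analysis plan is shown.

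- **Comparison between treatment arms.** Change to 6 months is analysed by "multiple regression analysis with 6-month mAQLQ as outcome and baseline mAQLQ as covariate along with arm of trial (intervention/control) in the model". All models are also adjusted for clustering within practices and for matching by size. The 3-month score is not a term in this model. Its stated use is separate, to decide when the outcome is best assessed: "Comparison of the mAQLQ scores at 3 months post-intervention as well as at 6 months post-intervention will enable us to establish the most appropriate time".
- **Trial procedures.** "Follow-up outcome questionnaires will be completed at 3 months and again at 6 months post review for all patients".
- **Withdrawal of patients from the study.** The fifth and last listed exit point is "prior to completing the 6-month follow-up questionnaires". A patient leaving there can have both a baseline and a 3-month score.
- **Missing data, mAQLQs.** The one rule given concerns missing items within a questionnaire: beyond a set number, "this patient will be excluded from the analysis". Nothing is said about a whole missing 6-month questionnaire.
- **Statistical analysis.** "The primary analysis will be a per protocol analysis based on an intention to treat".
- **Aims of the study.** Estimating the impact of the intervention on patient outcomes is a secondary aim.

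**The concern.** A regression with the 6-month score as outcome uses only patients who have that score. For a patient who leaves after 3 months, the trial holds a measurement taken under the allocated treatment and closely related to the missing one, yet the 6-month contrast ignores it. That sits badly with the reference to intention to treat.

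The loss could plausibly work differently in the two arms. Under Patient recruitment, the template covering letter tells patients which arm their practice is in. Under Trial procedures, only intervention patients complete a goal-setting tool, agree a plan built on it and receive a 6-week call about progress with that plan. A patient whose plan is not helping has a reason to stop responding that a control patient lacks. If such patients leave the intervention arm, those who remain look better than the arm as a whole, and the 6-month difference is too favourable.

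At stake is the accuracy of the estimated 6-month difference.

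**Working it through.** The article has no figure to reproduce: Sample size calculation says that no formal calculation was made, and the target is 8 practices x 10 patients = 80, about 40 per arm. The question is how far the stated model can be wrong, and under what conditions.

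**Inputs from the article:** the 6-month model; mAQLQ at baseline, 3 and 6 months; "A clinically relevant improvement is an increase of ≥0.5 in individual mAQLQ mean scores", used here as a yardstick; about 40 patients per arm.

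**Assumed, because the article gives none:** SD 1.0, the correlations, the withdrawal rates and the strength of the link between early response and withdrawal. Clustering is left out.

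**Two estimators of the 6-month arm difference**

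1. *Stated model.* In patients with a 6-month score, regress Y6 on baseline and arm, and take the arm coefficient.
2. *Model that also uses the 3-month score.* In all patients with a 3-month score, regress Y3 on baseline and arm, giving arm coefficient a. In patients with a 6-month score, regress Y6 on baseline, arm and Y3, giving arm coefficient g1 and Y3 coefficient g3. The estimate is g1 + g3 x a. This is the likelihood answer when withdrawal depends only on observed scores.

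**Check 1: when does bias arise?** Samples of 400,000, so the figures show bias rather than chance. Correlations: 0.6 between baseline and each follow-up, 0.7 between follow-ups. The log-odds of withdrawal change by 1 per point of change from baseline to 3 months. Bias of the stated model, in mAQLQ points:

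| Link between early change and withdrawal | True difference | 10% loss | 20% loss | 30% loss |
|---|---|---|---|---|
| None | 0 | -0.001 | 0.000 | 0.000 |
| None | 0.5 | -0.003 | -0.001 | 0.001 |
| Same in both arms | 0 | 0.005 | -0.001 | -0.003 |
| Same in both arms | 0.5 | -0.009 | -0.027 | -0.028 |
| Intervention arm only | 0 | 0.036 | 0.065 | 0.094 |
| Intervention arm only | 0.5 | 0.023 | 0.058 | 0.082 |
| Opposite in the two arms | 0 | 0.064 | 0.123 | 0.182 |
| Opposite in the two arms | 0.5 | 0.070 | 0.123 | 0.183 |

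The second estimator stayed within 0.007 of the truth in every cell. So dependence on early response is not enough: the dependence has to differ between arms before the bias matters.

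**Check 2: one concrete scenario.** Correlations 0.6 (baseline to 3 months), 0.55 (baseline to 6 months) and 0.7 (3 to 6 months); true difference 0.30. Loss after 3 months is 15-20% in the intervention arm, concentrated in poor 3-month scores (log-odds slope 1 to 1.5 per point), and 10% at random in controls. With 40 per arm that is 6-8 intervention patients (0.15 x 40 to 0.20 x 40) and 4 controls (0.10 x 40).

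- Stated model: bias about +0.05 (15% loss, slope 1) to +0.09 (20% loss, slope 1.5).
- Against the 0.5 threshold: 0.05 / 0.5 = 10% to 0.09 / 0.5 = 18%.
- With the 3-month score used: bias within 0.003.

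**Scale against chance.** In a 40 v 40 simulation without clustering, and with loss unrelated to response, the standard error was 0.205 for the stated model and 0.201 with the 3-month score, a gain of 0.004 / 0.205 = 2%. The bias in check 2 is 0.05 / 0.205 = 0.24 to 0.09 / 0.205 = 0.44 standard errors.

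**The case against.** A baseline-adjusted regression at one time point is a standard analysis, and the article never says that it will be restricted to complete cases. An unseen analysis plan could add imputation that uses the 3-month score. Part of this stands: silence on a missing visit is not itself a fault in a journal article. But the section introduces itself as the analysis plan and fixes outcome, patient-level terms and software. As written, that model cannot use a late withdrawer, and it would need amending or supplementing to do so.

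Three stronger readings are tempting, and none is supported.

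- *Any withdrawal related to early response invalidates the model.* It does not. With the same relation in both arms, the bias was at most about 0.03, even at 30% loss.
- *A biased effect is passed on to the full trial.* The article does not say so. What it takes forward is the variability of the main outcome, the ICC and the required sample size (Outcome measures; Comparison between treatment arms), and costs and QALYs for the value-of-information analysis (Cost-effectiveness). A 6-month variance or ICC from the same reduced set might be affected, but that was not examined here.
- *The trial expects substantial late loss.* It only lists points at which patients could withdraw. Retention is itself a pilot outcome, and Trial procedures offers postal or telephone completion, with telephone reminders for postal completion where needed.

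It also stands that the simulated withdrawal depends on the observed 3-month score, which is the mechanism the alternative model handles. If patients leave because they deteriorate after 3 months, that model is biased too. Late withdrawers still count in the separate 3-month comparison.

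**Conclusion.** The concern holds in a limited form. The stated 6-month regression does not use the 3-month scores of patients who withdraw between 3 and 6 months, and its estimate can be biased if that withdrawal depends on early response differently by arm. The range of about 0.05-0.09 points rests entirely on the assumed SD, correlations, loss rates and slopes of the concrete scenario. Opposite relations in the two arms, a more extreme assumption, gave about 0.06-0.18.

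In a pilot of 80 patients the scenario's bias is smaller than the sampling error, and it touches a secondary aim. The change is worth making because it is cheap, uses data already planned, and rests on a weaker assumption about missing scores. It would also try out that analysis in a study whose purpose is to pilot the design and process of a later trial.

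**What to change.** Replace the single-time regression under Comparison between treatment arms with one linear mixed model:

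- outcomes: mAQLQ at 3 and 6 months, as repeated measures;
- fixed terms: baseline mAQLQ, arm, time, arm-by-time, region and list size;
- patient and practice effects;
- both the 3-month and the 6-month arm contrasts reported from this model.

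Every patient with a baseline and at least one follow-up score then contributes in the allocated arm, and the comparison of time points comes from the same fit. Allowing the baseline coefficient to differ by visit would match the estimator checked above.

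The cost is one paragraph of analysis wording and no new data. The model is slightly more complex. It still assumes that loss is explained by the observed scores, and it does nothing for patients who leave before any follow-up questionnaire. Reporting the number lost after 3 months by arm, with their 3-month scores, would show how much the choice of model mattered.

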#### Cost-effectiveness

Cost-effectiveness of the asthma goal-setting tool will be measured as a cost per QALY [43]. The incremental cost-effectiveness ratio (ICER) will be estimated by dividing the difference in mean total costs between the intervention and control group by the difference in QALYs. Bootstrapping will be used to get an estimate of variability in the ICER. The economic analysis will include a VOI analysis [31]. The results of this analysis will indicate whether the data provided by the phase II feasibility trial are sufficient for decision-making and, if it is not sufficient, the optimal sample size of a future trial needed to provide additional information. The VOI analysis will be based on the estimates of the mean, variance and covariance of differences in costs and QALYs obtained from this phase II feasibility trial.

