**Methods/design:**

A two armed, single-blinded, multi-centre, cluster-randomised controlled feasibility trial will be conducted in UK primary care. Randomisation will take place at the practice level. We aim to recruit a total of 80 primary care patients with active asthma from at least eight practices across two health boards in Scotland (10 patients per practice resulting in ~40 in each arm). Patients in the intervention arm will be asked to complete a novel goal-setting tool immediately prior to an asthma review consultation. This will be used to underpin a focussed discussion about their goals during the asthma review. A tailored management plan will then be negotiated to facilitate achieving their prioritised goals. Patients in the control arm will receive a usual care guideline-based review of asthma. Data on quality of life, asthma control and patient confidence will be collected from both arms at baseline and 3 and 6 months post-intervention. Data on health services resource use will be collected from all patient records 6 months pre- and post-intervention. Semi-structured interviews will be carried out with healthcare staff and a purposive sample of patients to elicit their views and experiences of the trial. The outcomes of interest in this feasibility trial are the ability to recruit patients and healthcare staff, the optimal method of delivering the intervention within routine clinical practice, and acceptability and perceived utility of the intervention among patients and staff.

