### Allocation of trial interventions

The general practice is the unit of allocation. Central randomisation by the Tayside Clinical Trials Unit (TCTU) to intervention or control arms will be carried out separately for each of the two participating health board areas. This will be done using minimisation based on achieving optimum balance for practice list size (two strata <6,000 and >6,001 patients currently registered). The reason for randomisation by area is to ensure an even distribution of intervention and control practices as there is potential for geographical variation in asthma management strategies between health boards. Thus, within each area two large and two smaller practices will be matched to receive the intervention and control. TCTU will tell the research team of the outcome of the randomisation process and in turn the practices will be informed of their allocated group.

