### Recruitment

#### General practices and healthcare professionals

The Scottish Primary Care Research Network (SPCRN) will assist with practice recruitment by writing to the practices informing them of the study and enclosing an information sheet, an expression of interest form and a project practice consent form. Additional informal contact in the form of a project flyer will be made with practice nurses via the National Health Service (NHS) Education for Scotland (NES) education facilitators for the two regions. The Respiratory Managed Clinical Networks (MCNs) in both areas will be asked to bring the project to the attention of the practices. Interested practices will be asked to return the expression of interest form to the SPCRN administrator. A reminder letter will be sent by the SPCRN 4 weeks after the initial postal date with one follow-up phone call 2 weeks later. Active recruitment will cease once at least eight practices (four in each arm) meeting the eligibility criteria have been recruited. Once recruited, arrangements will be made with the practice manager and practice nurse to complete the signing of the consent form and to discuss the trial protocol, patient recruitment and arrangements for pre-study training. A folder containing the core trial documents will be given to each participating practice. This will include an algorithm for selecting patients, patient information and consent forms, the research team’s contact details and all trial information.

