### Outcome measures

The proposed outcome measures for the definitive trial have been chosen to reflect both clinical and patient-centred factors. The main primary outcome measure will be change in quality of life as measured by the mini Asthma-related Quality of Life Questionnaire (mAQLQ) [35]. The proposed secondary outcomes will include measures of asthma control, healthcare resource use, patient self-efficacy and cost-effectiveness. Asthma control will be assessed from the scores on the Asthma Control Questionnaire (ACQ) [38] and data from the Health Services Resource Use (HSRU) questionnaire. Cost-effectiveness will be measured as a cost per Quality-Adjusted Life Year (QALY) of the intervention compared to the control group. Utilising the HSRU data, the costs of overall asthma-related healthcare resource use over the 6-month pre- and post-trial period from an NHS perspective will be calculated. QALYs over the 6-month trial period will be derived from EQ-5D-3L responses [43]. The GOAL-setting process will be assessed by recording the number and type of goals identified and achieved. This information will be gleaned from the patient-completed goal setting tool and their level of confidence for achieving their identified goals from their completed action plan.

For this pilot trial, the key outcome measures of interest are aimed at enabling us to assess the feasibility of and plans for conducting the definitive trial:

• Practice and patient recruitment rates

• Retention rates

• Likely cost of the intervention

• Acceptability of GOAL tool and action plan process to adults with asthma

• The variability of the main outcome measure

• The sample size required to effect change in asthma-related quality of life

• Acceptability, effectiveness and ease of use of the chosen measuring instruments

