### Sample size calculation

As this is a feasibility study we have not undertaken a formal sample size calculation. A sample size of eight practices will allow for four practices in each health region. The aim will be to recruit approximately 80 patients in total (40 in each arm).

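### The economic section plans a bootstrapped ratio of unadjusted mean differences and does not carry the trial's clustering and baseline adjustment into the cost, QALY and value-of-information estimates; the cost window is also ambiguous

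*Protocol article*

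**What the plan says.** **Design.** Under Allocation of trial interventions, "The general practice is the unit of allocation". The recruitment section sets the number of clusters: "Active recruitment will cease once at least eight practices (four in each arm) meeting the eligibility criteria have been recruited". The abstract gives "10 patients per practice resulting in ~40 in each arm". There is no power calculation: "As this is a feasibility study we have not undertaken a formal sample size calculation".

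**Economic analysis.** The Cost-effectiveness section divides the between-arm difference in mean total cost by the difference in QALYs. For uncertainty it says "Bootstrapping will be used to get an estimate of variability in the ICER". No resampling unit, practice effect or covariate is named. On the next step it says "The VOI analysis will be based on the estimates of the mean, variance and covariance of differences in costs and QALYs". That analysis is to judge whether the pilot data suffice for a decision and, if not, how large the next trial should be. Aims of the study places it within the primary aim.

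**Time windows.** Under Outcome measures, asthma-related costs "over the 6-month pre- and post-trial period from an NHS perspective will be calculated", whereas "QALYs over the 6-month trial period will be derived from EQ-5D-3L responses".

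**Adjustment stated elsewhere.** Comparison between treatment arms, which concerns the mAQLQ, uses the baseline score as a covariate, adjusts all models for clustering and practice size, stratifies all analyses, and plans an ICC for every candidate outcome. Patient recruitment accepts that knowing the arm before consent could produce different kinds of participants in the two arms, and undertakes to control for any differences in the final analysis.

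**The concern.** The economic section describes a calculation on mean differences, not a model. A commitment to adjust models for clustering, placed in the mAQLQ section, therefore does not plainly reach it. Four things follow.

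- If variances are computed as though patients were independent, the standard errors of the cost and QALY differences are too small whenever outcomes are correlated within practices.
- A baseline difference in EQ-5D utility passes into an unadjusted QALY difference. The protocol itself gives a reason why such a difference could arise.
- The variability of a ratio has no clear meaning when its denominator is often near zero or of either sign. A negative ICER can mean that the intervention is better and cheaper, or worse and dearer.
- Costs are described over two periods and QALYs over one, and total cost is not defined.

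What is at stake is the VOI analysis. Variances that are too small make the pilot evidence look more certain than it is and lower the apparent value of further research. An imbalanced mean shifts the decision itself.

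**Working it through.** **The plan's own figure.** 8 practices × 10 patients = 80, or 40 per arm, as stated. The article gives no ICC, cost SD, QALY SD, willingness-to-pay value or VOI figure, so everything below rests on assumed ranges.

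**1. Clustering.** Design effect DE = 1 + (m − 1) × ICC with m = 10. The ratio of the naive to the correct standard error is 1/√DE.

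| Assumed ICC | DE | Naive/correct SE | SE too small by | Effective size of 80 |
|---|---|---|---|---|
| 0.01 | 1.09 | 0.958 | 4% | 73 |
| 0.02 | 1.18 | 0.921 | 8% | 68 |
| 0.05 | 1.45 | 0.830 | 17% | 55 |
| 0.10 | 1.90 | 0.725 | 27% | 42 |

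Trial status reports ten practices. If the 80 patients were spread over ten practices (m = 8), the shortfall would be 14% at ICC 0.05 (DE 1.35) and 23% at 0.10 (DE 1.70).

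A simulation with 4 practices of 10 per arm gave a patient-level bootstrap SE of 0.99, 0.91, 0.81 and 0.71 of the true SE at ICC 0, 0.02, 0.05 and 0.10. A plain practice-level bootstrap gave about 0.86 to 0.87 at every ICC. This matches the known factor √((k − 1)/k) = √(3/4) = 0.866 for k = 4 clusters per arm. Resampling practices does not on its own cure the problem.

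**2. Baseline utility.** With utilities at 0, 3 and 6 months and the trapezoid rule, baseline carries weight 0.25/2 = 0.125 year. For an assumed imbalance of 0.05:

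- no persistence: 0.05 × 0.125 = 0.00625 QALY
- full persistence: 0.05 × 0.5 = 0.025 QALY

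**3. Sign of the denominator.** Assume a 6-month QALY SD of 0.10, a true gain of 0.01 and ICC 0.05.

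- SE = 0.10 × √(2 × 1.45/40) = 0.0269
- P(estimated difference < 0) = Φ(−0.01/0.0269) = Φ(−0.37) = 0.355

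Without clustering the figure is 0.327. Over SD 0.05 to 0.125, gain 0.005 to 0.02 and ICC 0 to 0.05 it runs from 0.04 (SD 0.05, gain 0.02, ICC 0) to 0.44 (SD 0.125, gain 0.005, ICC 0.05).

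**4. Cost window.** If pre and post costs were added, with equal variances and correlation ρ, the variance of the cost difference would be 2(1 + ρ) times the post-only value:

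- ρ = 0.2: 2.4 (SE × 1.55)
- ρ = 0.5: 3.0 (SE × 1.73)
- ρ = 0.8: 3.6 (SE × 1.90)

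If pre-period cost serves only as a baseline, there is no mismatch.

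**5. Effect on VOI.** An illustrative normal model assumed a patient-level net-benefit SD of 2,000, mean incremental net benefit 100, 50,000 beneficiaries and a cost of 500 per trial patient, with DE applied to both the pilot and the new trial. The optimal number per arm was 390 when clustering is ignored and 410, 430 and 460 at ICC 0.02, 0.05 and 0.10. The increases are 20/390 = 5%, 40/390 = 10% and 70/390 = 18%. Varying the mean (0, 100, 300) and the beneficiaries (10,000, 50,000, 200,000) gave shifts from 5% (810 to 850) to 38% (130 to 180).

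**The case against.** The strongest reply is that a condensed article is being read too closely. The resampling unit is not stated, so a practice-level bootstrap is as consistent with the text as a patient-level one. The commitment to adjust all models for clustering, the stratification of all analyses, the promise to control for participant differences and the commitment to CONSORT for cluster trials may all be meant to cover the economics. Details of this kind often sit in a separate analysis plan.

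Much of that stands, and it rules out several stronger readings that a reader might infer:

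- *That the plan specifies a patient-level bootstrap, or rejects clustering and baseline adjustment.* It does neither; it leaves them unconnected to this section.
- *That costs and QALYs certainly span different periods.* The text says that costs are calculated over both periods, not that they are summed.
- *That the next trial's size would be built on the bootstrapped ICER.* The VOI uses the means, variances and covariance of the differences, so the objection to the ratio does not reach it. Comparison between treatment arms also gives a second route to sample size, through the ICCs.
- *That the net error in cost variance must be downward.* If pre and post costs were summed, the variance would move up, against the effect of ignored clustering.

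What the reply does not remove is the stated part of the method. The section defines the ICER as a ratio of plain mean differences and takes the variability of that ratio as its measure of uncertainty. It names no model to which the general clustering commitment could attach. Leaving the choice between bootstraps open is also not safe here, because with four practices per arm both simple forms are too narrow.

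**Conclusion.** The concern holds in a limited form. The economic section does not carry over the clustering and baseline adjustment that the article sets out elsewhere, relies on the variability of a ratio that will often be uninterpretable at this size, and leaves total cost undefined.

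The consequences are conditional. With patient-level variances the SEs would be about 4% to 27% too small for ICC 0.01 to 0.10, and there would be no such error at ICC 0. The QALY bias of 0.006 to 0.025 requires a 0.05 utility imbalance, which the article calls possible, not certain. Even so, the upper end exceeds the 0.01 gain assumed above. The 35% chance of a negative QALY difference depends on the assumed SD, gain and ICC.

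The VOI could be affected through its mean, variance and covariance inputs. The size of that effect cannot be fixed from the document; the 5% to 18% shift in the main illustration rests entirely on assumed values. The documents support saying that these estimates could be wrong, not that they would be.

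**What to change.** - Estimate incremental costs and QALYs jointly, with a practice effect and a small-sample correction suited to about four practices per arm. Do not rely on a plain practice-level bootstrap.
- Adjust QALYs for baseline EQ-5D utility, and costs for cost in the 6 months before the intervention.
- State that total cost in the ICER is the 6 months after the review plus the cost of the intervention, with pre-period cost used only as a baseline covariate. Reword Outcome measures and Cost-effectiveness to agree.
- Report incremental net monetary benefit, the cost-effectiveness plane and an acceptability curve. Give the ICER as a point value only.
- Feed the cluster-adjusted means and covariance matrix into the VOI.

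The resource-use and quality-of-life data needed are already planned for collection before and after the review, so no new data collection is called for. The cost is some extra analysis work and wider intervals, which better reflect what a pilot of this size can show.
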